## Abstract

**Background:**

Irritable bowel syndrome (IBS) is a common disease that affects the quality of life (QOL) and social functioning of sufferers. Visceral anxiety is currently considered a key factor in the onset and exacerbation of IBS, and cognitive-behavioural therapy (CBT) targeting visceral anxiety is thought to be effective. However, access to CBT is limited due to the lack of trained therapists, the substantial time required for therapy and the associated costs. Group CBT (GCBT) may solve some of these problems. We have therefore planned this trial to examine the efficacy of GCBT for IBS.

**Methods:**

The trial is a two-armed, parallel group, open label, stratified block randomized superiority trial. The study group will consist of 112 participants (aged 18–75 years) with IBS (Rome-III or IV criteria). Participants will be randomly allocated 1:1 to (i) the intervention group: ten-week GCBT plus treatment as usual (TAU) or (ii) the control group: waiting list (WL) plus TAU. The co-primary outcomes are the change in IBS severity or disease-specific quality of life from baseline to week 13 which is 1 month after the end of treatment. The efficacy of GCBT for IBS will be examined through mixed-effects repeated-measures analysis.

**Discussion:**

GCBT, if found effective, can address the issues of the shortage of therapists as well as the time required and the costs associated with individual CBT. Clinically, the findings will help make effective CBT programmes accessible to a large number of distressed IBS patients at lower costs. Theoretically, the results will clarify the relationship between IBS and psychological stress and will help elucidate the underlying mechanisms of IBS.

**Trial registration:**

UMIN, CTR-UMIN000031710. Registered on March 13, 2018.

## Background

Irritable bowel syndrome (IBS) is a common functional gastrointestinal disorder characterized by chronic or recurrent abdominal pain and altered bowel habits [1]. Its prevalence among the world population is as high as 10–15%, and IBS is a global health problem [2]. Although IBS is non-fatal, the symptoms affect quality of life (QOL) and social functioning [3] and lead to a health-care burden [4, 5]. Additionally, IBS typically develop in younger adulthood, an important period for education and career development. Thus, the corresponding socioeconomic impact of IBS is considerable [6].

However, there is no gold-standard therapy for IBS, and few options exist for patients who do not respond to available pharmacotherapies. Some psychotherapies, including cognitive behavioural therapy (CBT), hypnotherapy, and stress management therapy, have been proposed for IBS [7, 8]. In particular, CBT for IBS has been studied extensively and a systematic review has estimated the number needed to treat to be approximately 3 [95% CI, 2 to 6] [7]. Also, CBT is recommended in several international guidelines for IBS [9, 10].

Among the several programs reported as CBT for IBS, we focused on the interoceptive exposure-based CBT (CBT-IE) program [11]. CBT-IE was originally developed for panic disorder [12]. Patients with panic disorder are fearful of the sensations that are similar to those that they experience during their panic attacks, and tend to avoid the behaviours and activities that may cause them [13, 14]. These anxieties increase hypervigilance on somatic sensations and are linked to catastrophic thinking [15]. Consequently, even mild somatic sensations produce anxiety and the resultant anxiety intensifies the somatic sensations, thus creating a vicious circle of anxiety and somatic sensations [16]. These interactions between visceral anxiety and somatic sensations are very similar to those observed in patients with IBS [11, 16]. IBS patients show hypervigilance and hypersensitivity to visceral sensations, such as increased intensity of sensations and lowered thresholds for visceral pain [17, 18]. IBS patients often have exaggerated beliefs and anxiety about their symptoms, which make them consciously or unconsciously avoid situations causing the symptoms. Such avoidant behaviours may then increase anxiety, creating a vicious cycle of symptom exacerbation. Thus, CBT-IE approaches that target visceral anxiety using methods similar to those for panic disorder may be suited for IBS [11].

CBT-IE for IBS therefore includes exposure to visceral sensations, in addition to traditional CBT (such as psychoeducation, self-monitoring, cognitive reconstruction, attention training, and in vivo exposure) [11]. In the program, participants are encouraged to experience self-induced visceral sensations (eg, by putting ice on their abdomen) to reduce visceral anxiety. Such bidirectional interaction between somatic sensation and visceral anxiety is consistent with the concept of the brain-gut axis, which is considered to be the mechanism of IBS [19]. Thus, through the use of CBT-IE for IBS, we may be able to provide new insights into the brain-gut axis, a mechanism that plays an important role in the development and maintenance of IBS.

However, access to CBT for patients with IBS is limited due to the paucity of trained therapists, the lengthy time requirements for both the therapists and the patients, and the associated costs [20]. Given the large number of IBS patients and growing health care and social burden, it seems worthwhile to establish the effectiveness of the IBS Group CBT (GCBT). GCBT has been found to be effective in depression, panic disorder and other psychiatric disorders [21], and is attractive since it is cost and time effective [22].

Little is known about the effect of CBT-IE for IBS patients on a group basis. We will conduct a randomized controlled trial (RCT) to examine the efficacy of GCBT for IBS and this study will provide new insights into GCBT for IBS. Our programme aims to break the vicious cycle between anxiety, attention, avoidance behaviour, visceral sensations and disease severity. We will compare GCBT plus treatment as usual (TAU) against TAU alone. Our co-primary outcomes include disease-specific QOL and symptom severity of IBS at week 13 which is 1 month after the end of treatment.

## Methods

The study is a two-arm (allocation ratio 1:1), parallel group, waiting-list controlled, open label, stratified block randomized superiority trial. The reporting of this study protocol follows the Standard Protocol Items: Recommendations for Interventional Trials (SPIRIT) guideline [23] and the recent reporting guideline for interventions [24]. The study will be conducted in accordance with the Japanese Ethical Guidelines for Medical and Health Research Involving Human Subjects (December 22, 2014) and its guidance (revised February 28, 2017).

## Study setting

### Participants

Treatment will take place at the outpatient clinic of the Department of Gastroenterology, Kyoto University Hospital, Japan.

### Eligibility criteria

#### Inclusion criteria

The inclusion criteria are (i) the diagnosis of IBS by a gastroenterologist and medication history for more than 3 months; (ii) age 18–75 years; (iii) an IBS diagnosis according to Rome III or IV criteria* [25]; (iv) moderate or severe symptoms as defined by the IBS Severity Scoring System (IBS-SSS; scores of 175–299 indicate moderate severity, 300–500 indicate severe); (v) the ability to understand Japanese; (vi) the willingness to document bowel symptoms and medication use regularly and to complete the assessments; and (vii) the willingness to attend ten weekly sessions plus one booster session of GCBT.

All subjects will be informed that they should continue to receive usual care from their physicians and that no specific recommendations for changes in medications for IBS will be made by the research team.

Rome III or IV criteria*: In Japan, some patients are still diagnosed and treated according to Rome III, despite the 2016 revision of Roman IV. Thus, we will use both Rome III and IV criteria to include patients representing the IBS population in the clinical practices.

#### Exclusion criteria

The exclusion criteria are (i) patients with past or current psychotherapy**; (ii) outpatients in the psychiatric or psychosomatic medicine departments judged unsuitable for CBT by their doctor; (iii) patients at serious risk of suicide or self-harm as defined by a score of 2 or higher on item 9 of the Patient Health Questionnaire-9 (PHQ-9); (iv) patients who are pregnant; (v) patients with uncontrolled abdominal illness (e.g., active inflammatory bowel disease, liver or pancreatic disease); (vi) patients judged unsuitable for group therapy by the researchers; and (vii) patients who had experience of abdominal operation which had been thought to cause IBS.

Patients with past or current psychotherapy**: Psychotherapy for IBS is rarely practiced in Japan. In this study we aim to examine the benefits and harms of our program among typical patients who will be receiving psychotherapy for the first time. We will therefore exclude patients who have had past or current psychotherapy.

### Interventions

On the first day of trial participation, before randomization, all participants will receive psychoeducation about IBS treatment based on guidelines (e.g., lifestyle and diet, pharmacotherapy) from gastroenterologists [26].

### GCBT

The intervention consists of 10 weekly 90-min sessions with homework tasks and one booster session after 4 weeks. GCBT will be delivered face-to-face in groups of up to four participants and one or two therapists.

We prepared a manual translated into Japanese according to the Interoceptive Management for IBS programme by Craske et al. [11]. The original programme was designed for individual sessions, but with the permission of the original authors, we have modified the manual to accommodate group therapy and have prepared handouts for participants. The contents of the programme include the following:
Explanation of a psychological model of IBS. The effect of anxiety on gastrointestinal functioning and the role of conditioning in IBS. Patients record their own IBS-related behaviours (session 1).The role of awareness of IBS-related stimuli. Attentional control skills to learn how to shift attention away from rather than perseverate upon unpleasant visceral sensations (session 2).Explanation of the role of negative thoughts in exacerbating IBS (session 3).Explanation of how IBS-related avoidance and control behaviours maintain the fear and awareness of IBS symptoms (session 4).Interoceptive exposure (e.g., place ice on the stomach to cause abdominal symptoms similar to IBS symptoms) to reduce fear of the sensations (sessions 4 & 5).Exposure to feared/avoided situations in which IBS sensations are expected (sessions 4 & 5).
Reduction or removal of behaviours that serve to control symptoms, such as repeated toilet visits, avoidance of certain foods, and taking medications.Exposure to symptoms by engaging in activities that provoke symptoms, such as eating certain foods, physical activity, and stressful situations, attending a meeting when experiencing abdominal pain or riding the bus with fear of losing bowel control.Education for how to handle relapse (session 10).

Two therapists will conduct the GCBT treatment; one gastroenterologist with 13 years of experience in the treatment of IBS; and one clinical psychologist with 10 years of clinical experience. Both therapists had had little experience with GCBT with interoceptive exposure for IBS, and they have completed supervised GCBT training with a clinical psychologist who has extensive experiences with CBT for anxiety disorders in general and with CBT for IBS. All sessions will be performed using the treatment manuals that provide detailed guidance to standardize intervention during the study: the two therapists will also continue to receive supervision as needed through the current trial.

The participants allocated to the intervention group will start the GCBT immediately after randomization. They will concomitantly receive TAU from their general practitioner or gastroenterologist during the GCBT intervention.

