#### Waiting-list (delayed start) control group

The control condition of this study is a waiting list. During the waiting period, the participants will receive TAU and will also be asked keep an IBS diary for self-monitoring [27]. The participants in the control condition will receive GCBT after week 13.

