### Sample size

The sample size is based on the two co-primary outcomes of IBS-SSS and IBS-QOL. To adjust for multiplicity conservatively, we used the Bonferroni method and set the significance level at 2.5% (α level: 0.025). The correlation coefficient between the absolute scores of IBS-SS and IBS-QOL has been reported to be 0.36 [35]. With power set at 80% and α set at 0.025, for two co-primary outcomes correlating at 0.40, a sample size of 55 subjects per group is required to obtain sufficient power to detect a moderate effect size of 0.5 [43] between the groups. Because each randomization will take place for a group of 8 (4 being assigned to the intervention and 4 to the control), a minimum of 14 groups is required to reach this number, and the total sample size is therefore 8 × 14 = 112. With the mixed-effect models for repeated measures, we can obtain the same power with 30–50% fewer participants than with the ordinary t-test or analysis of covariance [44]. In this trial, less than 30% dropout is expected. We therefore set the final target sample size, including drop-outs, as 112 patients in total, or 56 patients in each group. The power calculations were conducted with SAS PROC POWER by an independent statistician (TS). The appendix shows the SAS program.

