### Statistical methods

All analyses will be performed according to the intention-to-treat principle; all participants will be included in their randomized groups whether or not they have received their allocated treatment.

The mean difference in change scores on the IBS-SSS and the IBS-QOL will be estimated by the mixed-effects model for repeated measures (MMRM) [45]. In this model, the scale scores at weeks 4, 9 and 13 are the dependent variables. The allocation group (intervention = 0 vs control = 1), measurement point (middle = 1, post = 2, follow = 3) and the interaction term of both factors are fixed effects. The measurement point is treated as a categorical variable. The baseline measurement is used as the covariate. A participant is taken as the random effect. The covariance matrix describes the correlation between observations at different measurement points [45]. The Hochberg method will be applied for adjustment of multiplicity, and the threshold for statistical significance will be set at *p* < 0.05 (two-sided).

Secondary outcomes, including GSRS, IBS-GIS, PHQ-9, GAD-7, EQ-5D-5 L and CPRS, are important to measure the wider IBS effects and will be similarly analysed (as appropriate for continuous or dichotomous outcomes). These analyses will be exploratory in nature to complement the primary analyses; therefore, we will not adjust for multiple testing.

In this trial, participants who attend at least 1–5 sessions will be defined as a ‘Completer’, and we will conduct an analysis of covariance (ANCOVA) using the completers’ data and check the robustness of the result by MMRM.

The follow-up assessments at week 27 will be descriptively compared with the assessments at week 13, as the randomized comparison between the two arms no longer holds after the control participants have received the GCBT.

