## Discussion

We have described the RCT protocol of GCBT with interoceptive exposure for IBS patients. The primary objective of this study is to evaluate the effectiveness of GCBT for IBS and contribute to the provision of a scientific basis for non-pharmacotherapy to treat refractory IBS. The study also has several secondary objectives, such as changes in anxiety and depression.

Group therapies are cost and time effective. In addition, group therapy has the advantage of allowing participants to interact with others with similar problems and are expected to have mutual support capabilities through sharing experiences and coping models in difficult situations among themselves [47, 48]. However, only a few randomized controlled trials (RCTs) of GCBT for IBS have been reported, and the IBS diagnostic criteria, control groups, and outcome measures used in each study were different. Moreover, two of the studies were small [49, 50], and one of them reported inappropriate randomization [49]. About the effectiveness of GCBT for IBS, their findings have been mixed [49–51]. Two RCTs confirmed the effect of GCBT for IBS; one study enrolled 47 IBS participants (diagnostic criteria by researchers) and found that GCBT was superior to the waiting-list group in alleviating abdominal complaints at 3 months [49]; another study randomized 23 IBS patients (Rome criteria) and found that GCBT produced greater reduction in gastrointestinal symptoms at 3 months than the home-based symptom monitoring with weekly telephone contact [50]. In contrast, a third study concluded that GCBT is not superior to an attention placebo control condition. The last study enrolled 210 IBS patients (Rome II criteria) and studied the effects of GCBT versus psychoeducational support versus intensive symptom and daily stress monitoring, on patients’ GI symptom for 3 months [51]: Both GCBT and psychoeducational support were significantly more effective than intensive symptom monitoring, but GCBT and psychoeducational support group did not differ.

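### The primary model and the sample size ignore therapy groups and randomization cohorts, so standard errors are misspecified and may be too small

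*Protocol article*

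**What the plan says.** All places are in the protocol article.

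- **Delivery (GCBT).** "GCBT will be delivered face-to-face in groups of up to four participants and one or two therapists". The same section adds: "Two therapists will conduct the GCBT treatment".
- **Control arm (Waiting-list control group).** "The participants in the control condition will receive GCBT after week 13". Until then these participants have usual care and a symptom diary, and no therapy group.
- **Cohorts (Sample size; Randomization and allocation concealment).** In the sample-size text, "each randomization will take place for a group of 8 (4 being assigned to the intervention and 4 to the control", and 14 such cohorts are needed. Up to eight people attend one psychoeducation session, are split at that cohort's median severity score, and are then allocated.
- **Primary model (Statistical methods).** Arm, measurement point and their interaction are fixed effects, with baseline as covariate. "A participant is taken as the random effect". The covariance matrix covers correlation between measurement points, that is, within a person.
- **Sample size.** The inputs are significance level, power, the correlation between the two outcomes (0.40) and an effect size of 0.5. There is no ICC or design effect. The groups serve only to round 55 per arm up to 56.
- **Expected interaction (Discussion).** Group participants "are expected to have mutual support capabilities through sharing experiences and coping models in difficult situations among themselves".

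**The concern.** The design is partially nested. Outcomes of people in the same therapy group may be correlated, and only the GCBT arm has such groups. The stated model has no term for this and treats the 56 GCBT participants as independent. The article itself names a mechanism for the correlation, and presents it as an advantage of group therapy.

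This is not a detail left to an analysis plan, because the article specifies the model and names its random effect. If therapy groups differ from one another, the stated model understates the variance of the GCBT mean. Confidence intervals are then too narrow and the nominal 5% may be exceeded. The trial succeeds if either co-primary outcome is significant, so the error rate of each test matters directly.

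**Working it through.** **1. Reproduce the stated sample size.** Inputs from Sample size: effect 0.5 SD, outcome correlation 0.40, and a Bonferroni level ("we used the Bonferroni method and set the significance level at 2.5% (α level: 0.025"). Statistical methods gives the two-sided threshold. Success needs at least one significant outcome.

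For independent observations, each test statistic has mean 0.5/√(2/n) and critical value 2.241. Power is the bivariate normal probability that at least one statistic exceeds that value.

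- Normal version: 53 per arm reach 80%; power is 81.8% at 55 and 82.5% at 56.
- t version (simulated): 54 per arm reach 80%; power is 81.1% at 55 and 81.8% at 56.

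The stated 55 is thus reproduced within two participants under independence, and it contains no hidden allowance for clustering.

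**2. When are the standard errors too small?** Let s be the variance of a cohort effect shared by both arms, g the therapy-group variance (GCBT arm only) and e the remaining variance. There are 14 cohorts with four per arm.

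- True variance of the arm difference: (g + e/4 + e/4)/14 = (4g + 2e)/56. The shared effect cancels.
- Variance from a model without these terms: (s + g + e)/56 + (s + e)/56 = (2s + g + 2e)/56.

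The true variance is the larger when 4g > 2s + g, that is, when 3g > 2s. If total variance is 1 in each arm, the ratio of true to model variance is 1 + 1.5g − s.

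**3. No shared cohort effect (s = 0).** g is then the ICC, which is assumed. The design effect in the GCBT arm is DE = 1 + 3 × ICC and the variance ratio is (1 + DE)/2. True error is 2 × [1 − Φ(z/√ratio)], with z = 1.960 for 5% and 2.241 for 2.5%. Power uses the method of step 1 with the variance of the difference multiplied by the ratio, at 56 per arm with no dropout.

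| ICC | DE | Ratio | Error at 5% | Error at 2.5% | Power, at least one outcome |
|---|---|---|---|---|---|
| 0 | 1.00 | 1.000 | 5.0% | 2.5% | 82.5% |
| 0.02 | 1.06 | 1.030 | 5.3% | 2.7% | 81.4% |
| 0.05 | 1.15 | 1.075 | 5.9% | 3.1% | 79.7% |
| 0.10 | 1.30 | 1.150 | 6.8% | 3.7% | 76.9% |
| 0.20 | 1.60 | 1.300 | 8.6% | 4.9% | 71.5% |

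**4. Family-wise error under the planned adjustment.** The article states: "The Hochberg method will be applied for adjustment of multiplicity, and the threshold for statistical significance will be set at" 0.05, two-sided. Simulating 14 groups of four against 56 unclustered controls, and ignoring the groups, gives a Hochberg family-wise error of 5.1% / 5.9% / 7.0% / 9.2% at ICC 0.02 / 0.05 / 0.10 / 0.20, against 4.8% without clustering. A test that respects the groups stays at or below 5%. Its power for at least one outcome is 80.8% / 79.0% / 75.7% / 70.0%.

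**5. With a shared cohort effect.** The ratio from step 2 gives, at nominal 5%:

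- s = 0.05, g = 0.05: ratio 1.025, error 5.3%
- s = 0.10, g = 0.05: ratio 0.975, error 4.7%
- s = 0.10, g = 0.10: ratio 1.050, error 5.6%

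Simulations agree: 5.2% to 5.4%, 4.8% to 4.9%, and 5.6%.

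**The case against.** The strongest objection concerns direction. Waiting-list participants have no therapy group, but they do belong to a cohort that was recruited, educated and randomized together with a GCBT group. Whatever a cohort shares cancels from the arm difference but stays in the stated model's residual variance, which makes that model conservative. Step 5 shows that this can offset the group effect or outweigh it. This stands. A reader might infer that the p-values are certainly too small; the documents give neither variance and do not support that. They do not show that the shared part is large either, and baseline adjustment may leave little of it.

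The second objection concerns size. At ICC 0.02 the effect is negligible. The article describes features that limit differences between groups: two therapists throughout, detailed manuals and continued supervision. Four is the maximum group size, and dropout below 30% is expected. With 30% of outcomes missing at random and no shared effect, simulated error was about 5.5% / 5.8% / 7.7% at ICC 0.05 / 0.10 / 0.20, against 5.8% / 6.6% / 8.4% with complete data. This also stands, and it makes the table in step 3 an upper case for each ICC.

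A third reply does not stand. The efficiency that the article claims for the repeated-measures model is no reserve for clustering: it already serves to avoid inflating the sample for dropout, and repeated measurements on one person do not remove variance between groups.

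**Conclusion.** The point holds as a conditional one and should be fixed. The stated model omits two features of the design, the therapy group in one arm and the randomization cohort across both, so its standard errors are misspecified. They are too small whenever 3 × group variance exceeds 2 × shared cohort variance.

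The error excess is slight at an ICC of 0.02 to 0.05 and becomes material from about 0.10 (6.8%, and 8.6% at 0.20). These figures assume no shared cohort effect, 14 full groups of four and no dropout, and the ICC values are assumptions throughout.

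A reader might also infer that the design fails to deliver its stated 80% power. The figures do not support that in general. At ICC 0.05 power is 79.7%, so 80% is essentially met before dropout. The fall from 82.5% is measured against a figure that the article never claims. A clear shortfall appears only at about 0.10 and above.

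**What to change.** In Statistical methods, for both primary models:

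- Add a term for cohort (the randomization block of up to eight) and a therapy-group random effect present only in the GCBT arm. Since each cohort forms one GCBT group, this is equivalent to a random cohort-by-treatment effect. The group effect alone would still omit the blocking.
- State whether the group effect may differ by visit. A constant effect forces the same between-group variance at week 4 as at week 13, the primary time point.
- Use Kenward-Roger or Satterthwaite degrees of freedom, and state in advance what is done if the variance estimate is zero, which can happen with 14 small groups.
- Report the estimated ICC.

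In Sample size, restate the power over an assumed ICC range, without enlarging the trial.

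The cost is mainly analysis wording, since group and cohort membership are known and no new data are needed. The downside is somewhat wider intervals, fewer degrees of freedom and a slightly lower stated power. The change should be made before the data are analysed, so that it cannot look driven by results.
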